## Abstract

**Background:**

Chronic suppurative otitis media (CSOM) is a significant health issue affecting Aboriginal Australians. Long-term hearing loss can cause communication problems, educational disadvantage, and social isolation. Current standard treatment for CSOM in our region is twice daily dry mopping of the pus from the ear canal followed by instillation of ciprofloxacin antibiotic ear drops for up to 16 weeks, or until the discharge resolves for a period of 3 days. The treatment is long, laborious and fails to resolve ear discharge in 70% of cases in remote communities. Bacterial pathogens also persist. Povidone-iodine ear wash is the preferred method of clearing ear discharge in Western Australia. However, evidence of its effectiveness is lacking. In systematic reviews, topical antibiotics (ciprofloxacin) have been shown to be more effective than oral antibiotics or topical antiseptics. Currently, it is unclear whether there are any benefits of combining these treatments.

**Methods:**

This protocol describes a 2 × 2 factorial randomised controlled trial of two different interventions (povidone-iodine ear wash and oral cotrimoxazole), given as adjunctive therapy to standard treatment for CSOM. 280 children, between 2 months and 17 years of age, Indigenous or non-Indigenous, living in participating Northern Territory (NT) communities are randomised to standard treatment (dry mopping and ciprofloxacin drops) plus one of two topical treatments (dilute povidone-iodine ear wash or no wash) and one of two oral medication treatments (16 weeks of cotrimoxazole or placebo).

**Discussion:**

Current treatment of CSOM in our region shows that eradication of bacterial pathogens from the middle ear space and dry ears is often not achieved. This trial will evaluate the efficacy of adjunctive treatments of antiseptic ear washes and oral antibiotics. Clinical, microbiological and hearing outcomes will be reported.

**Trial registration:**

This trial (ACTRN12614000234617) was registered with ANZCTR on 05 April 2014.

## Background

In 2013, remote Indigenous communities participating in ear and nasopharyngeal carriage surveillance found that around 50% of young children (mean age 13 months) had otitis media with effusion (OME), 37% had acute otitis media (AOM without perforation), and 12% had chronic suppurative otitis media (CSOM). [1] CSOM is one of the most significant health problems affecting young Aboriginal children in Australia today [2, 3] having compounding effects on hearing, behaviour and learning. It was not that long ago that children with pus draining from their ears were a common sight in remote communities with more than 50% of young children in some remote communities having long term CSOM. [4, 5] Although the rates of CSOM have decreased, the NT hearing service reported that 53% of young Aboriginal children living in remote NT communities still have some form of hearing loss. [6, 7] Of all forms of ear disease, children diagnosed with CSOM had the highest levels of hearing loss. It should be noted that children with dry perforations and wet perforations (or CSOM) may be interchangeable, depending on the season and the child’s upper respiratory infection status. Combined rates of wet and dry perforation between 2007 and 2011 were 26% (15 and 11%) in 0–5 year olds, 26% (10 and 16%) in 6–11 year olds, and 37% (12 and 25%) in 12+ year olds respectively [7]. While effective timely treatment of acute otitis media with perforation (AOMwiP) aims to prevent CSOM, the challenges involved in delivering appropriate treatment in remote settings mean that a large group of children develop chronic severe ear disease [8]. The early age of onset, the severity of the hearing loss, and the persistence of this infection, means that improving medical management for this condition is a priority. Once CSOM has become established, it is extremely difficult to treat. Ear discharge failed to resolve at the end of topical antibiotic therapy in 70% Indigenous children in our previous randomised trial. [9] While topical antibiotics have been shown to be more effective than oral antibiotics and topical antiseptics, it is unclear whether there are any benefits of combining these treatments [9–11]. Other treatment options, such as prolonged antibiotic intravenous treatment in hospital have not been used (or accepted) in the management of children from remote Aboriginal communities [12, 13]. Topical quinolone antibiotics (e.g. ciprofloxacin) are currently the recommended first line treatment for CSOM and are theoretically more active against the bacteria commonly associated with CSOM (*Pseudomonas aeruginosa*), but have failed to eradicate all pathogens involved (particularly *Staphylococcus aureus*). Our previous randomised trial comparing topical treatments, ciprofloxacin versus framycetin (0.5%), gramicidin, dexamethasone (sofradex®) for CSOM found that *Staphylococcus* species were the most commonly isolated pathogens in ear discharge after treatment (present in 75% of specimens). We also documented an as overgrowth of fungal species. [9] There are no large studies describing the microbiology of CSOM in Aboriginal children. There is also lack of evidence for the effectiveness of combining antiseptic ear washes (povidone-iodine) with topical antibiotics (ciprofloxacin or sofradex®). The only randomised controlled trial (RCT) in Aboriginal children to describe a treatment that was effective in the majority of children with CSOM (around 75%) used the combination of povidone-iodine ear washes followed by ciprofloxacin ear drops. However, there were important differences in the severity of disease in these children compared to those currently living in remote communities of the NT [14]. Based on the clinical trials literature, treatment with oral antibiotics is not recommended routinely for CSOM and are usually less effective than topical antibiotic treatment. In our most recent CSOM study, 75% of children who sought clinical care from their regular health care provider were prescribed amoxycillin. It is unclear whether this oral treatment is ever indicated. [15–17] The only published placebo-controlled trial found the addition of oral cotrimoxazole to topical aminoglycoside plus steroid treatment reduced persistent discharge by 25 and 15% after 6 and 12 weeks of treatment [18]. Currently, there is a preference for surgical repair of the tympanic membrane in older children with chronic perforations that are dry at time of surgery [19]. This RCT will determine the clinical and bacteriological efficacy of oral antibiotics and povidone-iodine ear washes in addition to current recommended treatment (dry mopping plus topical antibiotic drops). Outcomes after four months, and at 12 months follow-up will include degree of resolution of ear discharge, bacterial pathogen persistence, healing of the tympanic membrane and hearing levels.

## Methods

### Study design

This is a parallel group, 2 × 2 factorial design, randomised (allocation concealed), assessor blinded, controlled clinical trial. This RCT was conducted in the Northern Territory (NT) and aimed to compare current standard treatment (twice daily dry mopping, ciprofloxacin drops and weekly clinic review) with two adjunctive therapies. Each child was randomised to receive standard treatment plus one of two topical treatments (povidone-iodine ear wash or no ear wash) and one of two oral medication treatments (cotrimoxazole or placebo) for 16 weeks.

### Participants and setting

All children (Aboriginal and non-Aboriginal) aged 2 months to 17 years of age living in remote or urban NT communities with a tympanic membrane (TM) perforation and a diagnosis of CSOM in at least one ear were eligible. Children with the following were excluded: i) previously randomised in this study; ii) ciprofloxacin, cotrimoxazole or iodine allergy; iii) mastoid or tympanoplasty surgery in the preceding 12 months; iv) ear surgery scheduled in the next 4 months; v) congenital ear or hearing problems; vi) known immunodeficiency; or vii) pregnancy.

### Ethics, consent and permissions

This study was approved and reviewed six monthly by the Human Research Ethics Committee of the Northern Territory Department of Health and the Menzies School of Health Research (HREC-2014- 2170), and the Central Australian Human Research Ethics Committee (CAHREC-14-228). The trial was conducted in accordance with the principles of Good Clinical Practice (GCP), the Declaration of Helsinki and the National Health and Medical Research Council (NHMRC) recommendations for research in Indigenous communities. Each participating community council/board provided written approval of the study to the ethics committees. Freely given informed written consent was obtained in person, by the research nurses from every subject’s parent/guardian (plus assent from children over 10 years of age) prior to enrolment. The study information, provided face-to-face in written, oral, and pictorial formats have been approved by the Ethics Committees. An interpreter was used when requested (or deemed necessary by the researchers). Sufficient time was provided to ask questions, discuss participation with relevant others, and obtain further study details prior to signing and dating consent forms. Consent included permission for their child to have an ear examination, nasal and ear swabs, a general child health check at baseline, 4 and 12 months follow-up visits. Details of data collection at each of the scheduled assessment times are summarised in Table 1. Signed consent was also sought to access their child’s medical records, complete a lifestyle interview regarding information on likely risk or protective factors for otitis media, to use the study and standard medicines, and to be contacted by study researchers at the participant’s home and via phone or social media, for the duration of the clinical trial.

**Table 1 Tab1:** Schedule of assessments

Visit #	0	1	2	3
Event	^a^Screening	Day1	16weeks	12months
Informed consent				
Check informed consent				
Randomisation^b^				
Ear exam				
Check inclusion/exclusion criteria				
Nose and ear swabs				
Lifestyle questionnaire				
Clinical note review				
Check recent audiology				
General health check				
Record antibiotic/study medication use				
SAE reporting^c^				

^a^Screening is an ear exam to assess ear status and can occur on Day 1

^b^ Randomisation may be conducted at the time of screening

^c^Severe adverse events reporting will occur throughout the study

### Randomisation

Eligible children whose parent or guardian provided signed informed consent were randomised to one of the four treatment options according to a computer-generated sequence. This was obtained by a phone call (interactive voice response system) to the NHMRC Clinical Trial Centre (CTC). Children were stratified according to community and age (<4y, 4-10y, >10y) using a minimisation procedure**.** The allocation sequence was concealed from all investigators throughout the study. Study staff were blinded to the oral component of the treatment at randomisation and follow-up assessments. However, it was not possible to blind the topical treatment groups. All laboratory staff are blinded. The randomisation of an individual participant would only be unblinded in emergency situations where the chief investigator and study’s medical monitor feels the emergency cannot be adequately addressed without knowing which treatment was delivered.

### Intervention

Intervention 1: The active oral medication used for this trial is cotrimoxazole suspension (or tablet for children over 12 years of age). A non-active formulation of the exact colour, taste and appearance as the intervention was used as the placebo. Cotrimoxazole suspension was given as 4 mg/kg per dose (of trimethoprim component) twice a day orally for 16 weeks. The placebo was administered in an identical manner.

Intervention 2: The topical treatment was aqueous povidone-iodine 10%, diluted in clean, room temperature water (1:20). Each discharging ear was syringed twice daily using a 20 ml syringe for up to 16 weeks or until the ear was dry for 14 days (confirmed on two clinical examinations 1 week apart by study or clinic staff). Treatment was recommenced if discharge becomes present again.

### Safety monitoring

Serious adverse and medically significant events including reactogenicity were regularly monitored. Serious local or systemic reactions were noted at the time of randomisation, on day three and regularly throughout the trial by reviewing all presentations to the clinic and hospital and asking standardised questions (in person or by phone call) to the families. All adverse events were reviewed by an independent data safety monitory board (iDSMB), and reported to the ethics committees. The iDSMB, its quorum and detailed study stopping rules were established prior to the commencement of the study and are included in the study protocol. No modifications to the protocol would be made without the approval of the chief investigator and communication with all investigators and other adjudicating bodies including the iDSMB, ethics committees and Indigenous reference group.

### Outcome measures

The primary outcome measure was the proportion of children with clinical failure after 16 weeks (4 months) of treatment. Clinical failure was determined by clinical examination for the presence of any ear discharge. Additional secondary outcome measures at 4 months and 12 months included: i) hearing level, determined by audiometry (performed by trained audiologists) and summarised as the pure tone 4 frequency average hearing level at 500, 1000, 2000 and 4000 Hz in the better and worse hearing ears; ii) failure to improve (determined by perforation size and amount of discharge); iii) change in perforation size and amount of discharge (determined by comparison of standardised assessment at baseline with end of study); iv) time to cessation of discharge (determined by review of health records); v) adherence to recommended management including attendance for specialist review (determined by review of health records); vi) presence of recognised bacterial pathogens in nose and ear discharge (determined by standard microbiological culture and antimicrobial sensitivity methods); vii) complications (defined as development of a related illness requiring additional medical treatment); and viii) side effects (defined as development of illness requiring cessation of prescribed treatments). Additional secondary outcomes at 4 months and 12 months from randomisation included the proportion of children with any carriage of pneumococci and any carriage of vaccine or non- vaccine serotype pneumococci and any carriage of NTHi. All children were followed up for any adverse events (AE) and serious adverse events (SAE) by reviewing the child’s clinic and hospital records and asking the parents about any side effects of the treatments between and at visits. We documented any contact the family or child had during the study with the clinic or hospital, including all relevant investigations and treatments. Regular, scheduled home visits, phone calls, SMS texts and social media contact with the families were made and recorded by study nurses or community researchers to support and promote participant retention; and monitor adherence.

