#### Audiology outcomes

Differences in hearing level at 12 months will be assessed using a simple linear regression. The absolute mean difference and the 95% confidence interval between the two interventions will be reported. The baseline hearing level will be adjusted in an analysis of covariance (ANCOVA). Further, the stratification factors and the other intervention will be included as explanatory variables to assess their effects on the hearing outcome.

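### Hearing is summarised only by better and worse ear, so neither summary follows the ear with CSOM that is washed; add an analysis of that ear alongside them

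*Protocol article*

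**What the plan says.** Four statements in the protocol article bear on this.

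- **Outcome measures** makes hearing a secondary outcome: "Additional secondary outcome measures at 4 months and 12 months included: i) hearing level, determined by audiometry". The result is "summarised as the pure tone 4 frequency average hearing level at 500, 1000, 2000 and 4000 Hz in the better and worse hearing ears". No summary is defined by which ear had CSOM.
- **Participants and setting** admits unilateral disease: children with "a diagnosis of CSOM in at least one ear were eligible".
- **Intervention** gives the wash by ear: "Each discharging ear was syringed twice daily using a 20 ml syringe for up to 16 weeks", or until the ear has been dry for a set period. Cotrimoxazole or placebo is given to the whole child, "twice a day orally for 16 weeks".
- **Audiology outcomes** sets out the analysis: "Differences in hearing level at 12 months will be assessed using a simple linear regression". It then adjusts for baseline hearing by ANCOVA and adds the stratification factors and the other intervention. It does not name the ear.

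**The concern.** The ear that enters each hearing summary is chosen by how well it hears, not by whether it was diseased or washed. In a child with one diseased ear this has two consequences.

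- **Better ear.** It is mostly the ear that had no CSOM and was not washed. A local treatment has little chance to show an effect there.
- **Worse ear.** It is usually the CSOM ear. If the wash improves that ear beyond the level of the other one, the other ear becomes the worse ear and the rest of the gain is not counted.

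Better and worse are labels that can also move between ears from one visit to the next. If they are reassigned at each visit, the baseline covariate and the follow-up value may come from different ears, and some of the precision expected from ANCOVA is lost.

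At stake is interpretation. Hearing loss is the harm that motivates the trial. A small or null difference on these summaries could be reported as no hearing benefit from the wash, although the washed ear was never analysed as such.

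**Working it through.** **The plan's own figure.** The only stated size is 280 children for the primary outcome. With 70% against 50% failure, two-sided 5%, 90% power and no continuity correction, the requirement is 124 per margin. Allowing for 10% loss, 124 / 0.9 = 137.8, so 138 per margin and 276 in total, which agrees with 280. With 252 evaluable (126 per margin) power is 90.5%. This concerns child-level discharge, and the hearing question does not touch it.

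**Inputs for hearing.** The documents give no hearing SD, expected gain, between-ear gap, correlation, unilateral share or number tested. All of the following are assumptions: CSOM ear mean 40 dB; other ear 5 to 20 dB better in unilateral children; SD 12 dB in each ear; between-ear correlation 0.4; true gain 5 dB in every CSOM ear and none in the other ear; 30% to 70% unilateral. For power only: 100 tested children per margin and baseline to follow-up correlation 0.6.

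**Step 1, unilateral children.** Let D be the loss in the CSOM ear minus the loss in the other ear. It is normal with mean g (the gap) and SD s = 12 × √(2 × (1 − 0.4)) = 13.15. Write E(m) = m·Φ(m/s) + s·φ(m/s) for the mean of the positive part of D when its mean is m. The gain seen in the worse ear is E(g) − E(g − 5). The gain seen in the better ear is 5 minus that.

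- Gap 20 dB: E(20) − E(15) = 20.37 − 15.83 = 4.54 in the worse ear, leaving 0.46 in the better ear.
- Gap 5 dB: E(5) − E(0) = 8.12 − 5.24 = 2.88 in the worse ear (2.875 before rounding), leaving 2.12.

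**Step 2, all children.** In bilateral disease both ears gain 5 dB, so both summaries show 5. With unilateral share u, the average is (1 − u) × 5 + u × (step 1 result).

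| Gap | Unilateral | Worse ear (dB) | Better ear (dB) |
|---|---|---|---|
| 20 dB | 30% | 4.86 | 3.64 |
| 20 dB | 70% | 4.67 | 1.83 |
| 5 dB | 30% | 4.36 | 4.14 |
| 5 dB | 70% | 3.51 | 2.99 |

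The worse ear loses 3% to 30% of the 5 dB and the better ear 17% to 63%. The largest better-ear loss (gap 20 dB, 70% unilateral) goes with a worse-ear loss of only 7%.

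**Step 3, power.** Simulated ANCOVA under the same assumptions gives about 24% to 89% for the better ear, 80% to 97% for the worse ear and 97% to 99% for the CSOM ear or ears. The last range averages both ears in bilateral children, which itself reduces variance. With one fixed CSOM ear per child it is 94% to 97%.

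**Step 4, which ear is worse at follow-up.** In washed unilateral children the other ear is the worse one with probability 1 − Φ((g − 5)/s): 13% at a 20 dB gap and 50% at 5 dB. With no treatment effect, 1 − Φ(g/s) already gives 6% and 35%. The shift due to treatment is the difference, about 6 to 15 percentage points.

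**A second set of assumptions** points the same way. With CSOM ear mean 30 dB (SD 12), other ear mean 10 to 25 dB (SD 10), correlation 0.4 and half the children unilateral, the worse ear shows 4.8 to 4.0 dB of 5 and the better ear 2.7 to 3.6 dB.

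**The case against.** The strongest reply is that the plan reports both ears, and in unilateral CSOM the worse ear is usually the washed one. Where the other ear is clearly healthier, the worse-ear summary keeps more than 90% of the effect. That stands, and it rules out the reading that the hearing effect is lost under the plan as a whole.

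Second, this is partly a choice of estimand. The child is randomised, the primary outcome is by child, and communication and schooling depend on how the child hears. A smaller better-ear effect answers a different and legitimate question. That also stands, and it argues against replacing the child-level summaries.

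Third, cotrimoxazole is systemic, so there are no untreated ears in that comparison. Dilution would arise there only if benefit were confined to diseased ears. The ear with CSOM at baseline is also not exactly the ear washed, because the wash follows discharge and is restarted if discharge returns.

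Fourth, a reader might infer that the ANCOVA uses the wrong ear's baseline. The article does not say so. It names no ear, and that detail may be settled in the full protocol or analysis plan. A reader might also take 13% to 50% as the share of children whose ears switch because of treatment. Step 4 shows that most of that share would exist without any effect.

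What survives is that neither stated summary is tied to the diseased, washed ear, and that nothing in the article supplies one that is.

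**Conclusion.** The point holds in a limited form. For the wash comparison in unilateral disease, the better-ear summary mostly reflects an unwashed ear and can lose much of a real gain: 17% to 63% over all children in the illustration. The worse-ear summary loses a small to moderate part, 3% to 30%, and the two losses are not greatest in the same setting. These sizes rest wholly on assumed values. If few children have unilateral disease the loss is slight, and in bilateral disease with equal gains there is none.

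The documents do not support a claim that the hearing analysis is invalid, that both summaries are badly diluted together, or that the oral comparison suffers in the same way. Hearing is secondary, so the sample size and the primary conclusion stand. This is an inexpensive improvement to what the trial can say about the wash and hearing, not the correction of an error.

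**What to change.** Keep the better-ear and worse-ear summaries. Add one prespecified analysis of the four-frequency average in the ear or ears with CSOM at baseline, adjusted for the same ear's baseline value, both interventions and the stratification factors (age group and community). For bilateral cases use a linear mixed model with a random child effect, or the mean of the two ears. State that this analysis is the one used to interpret the effect of the wash on hearing, and that the better-ear average is the child-level functional result.

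The change needs wording in the analysis plan and a little programming. The Trial status section reports data collection and cleaning still under way, so it can be recorded before the hearing data are analysed. Ear-specific thresholds are already needed to name a better and a worse ear, so no new measurement is required. The price is one more secondary hearing estimate, and children without ear-specific thresholds cannot enter it.
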